#### Analysis of Data

Detailed description of statistical analyses will be found in the respective scientific publications. In general, for parametric data displaying a normal distribution, results will be presented as arithmetic means with SDs. For data showing a skewed distribution, as is commonly found for exposure measurement data, the results will be presented as geometric means with geometric SDs. Categorical data will be presented as percentages. In case of missing variables, omission or imputation will be performed depending on the type of data.

In general, risk estimates for the various outcomes with 95% CIs will be estimated using a regression model being appropriate for the analysis in question. The estimates will be adjusted for covariates identified as potential confounders, effect modifiers, and mediators. Tests are considered statistically significant at a *P* value of .05.

Analyses related to the intervention study will be performed according to intention-to-treat, regardless of protocol adherence. Results will be reported in line with CONSORT (Consolidated Standards of Reporting Trials) guidelines.

#### Intervention Outcomes

The primary outcome, outcome measure (OM) 1, is to evaluate the effect of the interventions (control measures) on reducing salmon processing workers’ personal exposure to airborne inhalable total protein (µg/m^3^) from T_1_ to T_2_. Differences in mean concentration of full shift measurements (8 hours) between intervention groups and between intervention groups and control groups will be analyzed.

The secondary outcome measures are the changes from T_1_ to T_2_ for a range of other exposure and health outcomes. Differences between intervention groups and between intervention groups and control groups will be analyzed. The following secondary outcomes will be assessed:

OM 2: Change of concentration of salmon processing workers’ personal exposure to proteases (ng/m^3^).

OM 3: Change in total protein (µg/m^3^, inhalable aerosol fraction) from stationary measurements in relevant areas of the salmon production line.

OM 4: Change of salmon processing workers’ personal exposure to airborne fish allergens, measured by concentration of total aerosol fraction of fish allergens (ng/m^3^).

OM 5: Change of salmon processing workers’ personal exposure to airborne endotoxins (EU/m^3^).

OM 6: Change in salmon processing workers’ self-reported symptoms from the upper airways.

OM 7: Change in salmon processing workers’ self-reported symptoms from the lower airways.

OM 8: Change in salmon processing workers’ self-reported eye symptoms.

OM 9: Change in salmon processing workers’ lung function at group level (FEV_1_ in percentage of predicted value).

OM 10: Change in salmon processing workers’ lung function at individual level (FEV_1_/FVC ratio).

OM 11: Change in salmon processing workers’ cross-shift lung function (FEV_1_).

OM 12: Change in salmon processing workers’ cross-week lung function (FEV_1_).

OM 13: Incidence of salmon processing workers’ sensitization to salmon assessed by serum IgE specific to salmon proteins.

OM 14: Change in salmon processing workers’ self-reported skin symptoms.

For more details regarding the intervention study, please see ClinicalTrials.gov NCT05039229.

### Other Outcomes of Interest (Substudies)

In addition to outcome measures related to the intervention study itself, substudies will investigate the following:

Characterization of airborne bioaerosols from the work environment with respect to inhalable protein, protease enzymes, microorganisms, and microbially derived agents, as well as known and possible novel fish allergens.Development of improved test extracts for seafood allergy diagnosticsExposure-response relationship between bioaerosol exposure and indicators of respiratory health effects, markers of inflammation, and sensitization.Identification of factors that can explain the variation in bioaerosol exposure (determinants of exposure).Evaluation of prevalence and determinants of respiratory work-related symptoms and disease.Evaluation of prevalence of work-related asthma by assessment of respiratory symptoms and work-related airflow limitation by serial measurements of PEF.Cross-shift and cross-week changes in acute symptoms from airways and eyes, as well as inflammatory biomarkers.Status of markers of inflammation and sensitization among salmon processing workers.Presence of indicators of health-promoting working environments in the salmon processing industry, demographical differences in perception, and their consistency through a 1-year follow-up.Evaluation of prevalence and determinants of dermatological work-related symptoms and disease.Objective evaluation of hand eczema and skin barrier function.Investigation of which indicators of health-promoting working environments are present in the salmon processing industry, and whether these are consistent through a 1-year follow-up.Associations between employment conditions and health among migrant workers.

### Participant and Public Involvement

Participants and the public have been involved in the design of and recruitment for the study by personal contact and through the reference group. They will be further involved in dissemination activities to ensure that information is given in a way that is clear and easy to understand for the different stakeholders.

### Reference Group

The reference group’s mandate is to ensure that the project is relevant for the salmon processing workers, is professionally sound and anchored within the industry, and that it is practically feasible and adequately prioritized. Its main role is to give advice in terms of planning, executing, and possibly adjusting the project. The group’s purpose it to ensure good collaboration with those who can profit from the project’s results, to root the project in the participating factories, as well as to give advice in terms of communication. The reference group does not have any responsibility for the project’s progression, goal achievement, or formalities; neither does it have any authority to take decisions. It consists of members of the employer organization the Norwegian Seafood Federations (Sjømat Norge), the employee organization Norwegian Food and Allied Workers Union (Norsk Nærings- og nytelsesmiddelarbeiderforbund), the Norwegian Labour Inspection Authority, an occupational health service, 1 plant representative from each of the 3 geographical regions, 1 researcher from each of the project group’s locations (Tromsø, Bergen, Trondheim), and the principal investigator.

## Results

The study was originally planned to begin in fall 2020 but was delayed to September 2021 due to the COVID-19 pandemic. The pandemic further influenced both data gathering and company access due to access restrictions and short-notice sick leaves or quarantines. Among other consequences, this led to delays in baseline measurements, especially in the plants in mid-Norway that had carried out their baseline measurements (T_1_) between March and June 2022, 3 months behind schedule.

As the study is still ongoing and data quality checking is not finished, we only have preliminary results from the baseline measurements at T_1_. The main questionnaire at T_1_ was answered by 740 participants. Due to uncertainties in numbers of distributed questionnaires, it was not possible to calculate a precise response rate, but we estimated its average to be 61% with a range between about 48 (31%) out of 155 and 134 (91%) out of 147. A total of 673 workers participated in the baseline health examinations. Calculating the participation rate is futile, because in several plants there was a much higher number of potential participants than there was capacity to carry out health examinations.

Exposure measurements were undertaken, resulting in over 700 personal measurements (400, 203, and 122 for protein, allergens, and endotoxins, respectively), as well as almost 150 stationary measurements (59, 51, and 34 for protein, allergens, and endotoxins, respectively).

Due to a long time frame of about 2 years between the companies’ original consent to participate in the trial and the actual start of the study, technical adjustments were done in several factories before the study start. Thus, the original plan to allocate 3 plants per intervention group was not feasible. One plant planned adjustments to the ventilation system during the intervention period and was therefore not allocated to any of the original intervention groups at T_0_. This left only 2 groups for the CS arm, while 3 plants each were allocated to the NZ and control group arms.

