### Specifics for the Intervention Trial

The core of the study is a pragmatic parallel group, 3-arm nonrandomized multicenter superiority trial with a 1:1:1 allocation ratio (ClinicalTrials.gov NCT05039229).

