#### Assignment of Intervention

Randomization of intervention arms was not feasible because of different premises of plant infrastructure. The participating plants were therefore allocated to the study arms by the project group, based on meetings and discussion with the local staff and management, and aiming at covering all 3 study arms in each region. Criteria that were taken into account for allocation to a specific arm were prestudy status of awareness and compliance of bioaerosol-reducing behaviors and technical installation, such as use of swabbing; flushing of work areas during work shifts; number, type, and shielding of water nozzles; water pressure; ventilation system; and plans for any alteration of these factors within the study period.

Allocation concealment and blinding was not relevant for obvious reasons.

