### Statistical Analysis

#### Sample Size and Power Analysis

Statistical power was estimated according to the primary outcomes of the project: the change in exposure to inhalable total protein in the breathing zone before T_1_ and after T_2_ and implementing exposure-reducing interventions in the participating salmon processing factories. A previous study in the Norwegian salmon industry reported a geometric mean exposure of total protein in the processing areas of 2.7 (range 0.76-12.62) µg/m^3^ [4]. The study was based on 273 exposure measurements, making it the most extensive study available on assessment of the concentration of total proteins in the salmon processing workers’ breathing zone. The crude data allowed us to estimate the corresponding arithmetic mean exposure of total protein (10.0, SD 5.8 µg/m^3^). Based on these data we estimated that with a significance level of .05 there is a power of 80% of finding a 40%, 30%, and 20% reduction of exposure in 1 intervention arm if we include 34, 59, and 133 measurements in each of the groups, respectively. Since baseline measurements are performed at all sites before intervention, there will be an even higher statistical power given that we can adjust the exposure levels after intervention for mean baseline values at each site. Based on these calculations, we aimed at including 24 workers with 2 repeated measurements in each of the intervention groups (144 measurements in each group equals a total of 432 measurements) both at baseline and after intervention.

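### The 1:1:1 ratio, the 144 measurements per group and the 20% power scenario were not reconciled with the actual 3:2:3 plants, so both CS contrasts have about 74% rather than 83% power for a 20% reduction

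*Protocol article*

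**What the plan says.** Under Specifics for the Intervention Trial, the article calls the study a "3-arm nonrandomized multicenter superiority trial with a 1:1:1 allocation ratio".

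Under Sample Size and Power Analysis, it takes an arithmetic mean of 10.0 and an SD of 5.8 µg/m³ for total protein and states that "with a significance level of .05 there is a power of 80% of finding a 40%, 30%, and 20% reduction of exposure" is available in one intervention arm with "34, 59, and 133 measurements in each of the groups, respectively". The recruitment aim is "24 workers with 2 repeated measurements in each of the intervention groups", expanded as "144 measurements in each group equals a total of 432 measurements", at baseline and again after intervention. It adds, without a figure, that adjusting for each site's mean baseline value will raise power further.

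Under Eligibility and Exclusion Criteria, individual exposure assessment is capped at 24 workers per plant. Under Assignment of Intervention, plants were allocated "aiming at covering all 3 study arms in each region".

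The Results section reports that technical changes made before the start ruled out three plants per arm. One plant was planning ventilation work and went into none of the original groups. The outcome: "This left only 2 groups for the CS arm, while 3 plants each were allocated to the NZ and control group arms".

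Under Intervention Outcomes, the primary outcome is compared between the intervention groups and between each of them and control. That makes three contrasts: NZ v control, CS v control and NZ v CS.

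**The concern.** The ratio, the sample size and the power scenarios describe nine plants in three equal arms. The Results describe eight plants in arms of 3, 2 and 3, with a ninth outside. Nothing in the article carries the second description back to the first. A reader who takes the sample size section at face value would credit all three primary contrasts with 144 measurements a side and at least 80% power for a 20% reduction. For the two contrasts that involve CS, the plant cap makes that size unreachable.

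A null CS result could then be read as evidence against a reduction of 20% when the comparison was less able to show one than stated. The aim of having every arm in every region is also affected, since two CS plants cannot cover three regions.

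**Working it through.** **Inputs.** Mean 10.0 and SD 5.8 µg/m³, α = .05, power 80%, stated n of 34, 59 and 133, target 144 per group (Sample Size and Power Analysis). Cap of 24 workers per plant (Eligibility and Exclusion Criteria). Arms of 3, 2 and 3 plants (Results). The article does not say whether α is one- or two-sided.

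**Step 1: reproduce the stated figures.** For two independent means, n per group = 2(1.960 + 0.8416)² × 5.8² / δ² = 528.07 / δ², rounded up.

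- 40%, δ = 4: 528.07/16 = 33.005, so 34.
- 30%, δ = 3: 528.07/9 = 58.67, so 59.
- 20%, δ = 2: 528.07/4 = 132.02, so 133.

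All three match. A one-sided α would give 26, 47 and 104, so the plan used a two-sided test, equal groups and independent measurements.

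**Step 2: reproduce the target.** 24 × 2 = 48, which is 144 only if read per plant with three plants per arm: 3 × 48 = 144, and 3 × 144 = 432.

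**Step 3: apply the actual allocation.** CS: 2 × 48 = 96 per visit at most. NZ and control: 144 each. Three arms: 8 × 48 = 384. The CS ceiling of 96 is below the plan's 133.

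**Step 4: power.** SE = 5.8 × √(1/n₁ + 1/n₂); power = Φ(δ/SE − 1.960).

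- 144 v 144: SE = 0.6835. For δ = 2, Φ(2.926 − 1.960) = 83.3%.
- 96 v 144: SE = 0.7642. For δ = 2, Φ(2.617 − 1.960) = 74.4%. For δ = 3, 97.5%. For δ = 4, 99.95%.

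The noncentral t gives 83.1% and 74.1% for the 20% reduction, and 97.4% and 99.9% for 30% and 40% at 96 v 144.

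**Step 5: detectable reduction at 80% power.** 2.8016 × SE is 1.915 for 144 v 144 (19.1%; 19.2% by noncentral t) and 2.141 for 96 v 144 (21.4%; 21.5% by noncentral t). With 144 in the comparator, CS would need 122 measurements to regain 80% at a 20% reduction.

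**Step 6: baseline adjustment.** If adjustment multiplies the residual SD by √(1 − r²), 80% power needs SE = 2/2.8016 = 0.7139. Then 1 − r² = (0.7139/0.7642)² = 0.873 and r = 0.36 (0.37 by noncentral t). The article gives no correlation. For assumed values at 96 v 144, power for a 20% reduction is:

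| r | Power |
|---|---|
| 0.2 | 76.1% |
| 0.3 | 78.3% |
| 0.4 | 81.5% |
| 0.5 | 85.6% |

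**Step 7: baseline counts, as a sensitivity check.** The Results give 400 personal protein measurements at baseline, a preliminary figure. If they were spread evenly over nine plants (an assumption), each plant has 44.4, CS has about 89 and the other arms about 133. Power for a 20% reduction in a CS contrast is then about 71%.

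**Step 8: regions.** There are three regions and two CS plants, so at least one region has no CS plant. The article does not say which.

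**The case against.** The strongest reply is that nothing is miscalculated or hidden. The figures 34, 59 and 133 are correct, and the 80% is conditional on reaching them. The 144 and the regional coverage are worded as aims, and the Results openly give the departure. A planned design followed by a declared deviation is a normal layout for an article on an ongoing study. The loss is small, touches only the smallest of three scenarios, and might be recovered by baseline adjustment.

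Most of this stands. It limits the point to a failure to reconcile sections. It does not remove it: the 1:1:1 ratio is stated flatly as a feature of the trial, and no section says what the lost CS plant does to n or power. The adjustment argument is a possibility only, since the article gives no correlation and mentions only site means. An unseen analysis plan would not cure figures that conflict within this document.

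A reader might infer more, in four directions that the article does not support.

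- **Near-total loss of power.** Treating plants as the units gives about 44% for 2 v 3 plants at a 20% reduction, even with no within-plant correlation. The intended 3 v 3 comparison gives only 60% on that basis, so most of the drop comes from the change of unit and not from the missing plant.
- **Confounding with the late mid-Norway baselines.** The region without CS is not identified, and follow-up is planned for about the same time of year, which limits seasonal bias in within-plant change.
- **NZ v control should become the main contrast.** Re-ranking the comparisons after allocation is a design preference.
- **CS should be compared only within regions that have a CS plant.** This too is a preference, and it would leave fewer plants.

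**Conclusion.** The point holds, with moderate weight. The stated ratio, the per-group number and the 20% scenario do not describe the trial as allocated. For CS v control and CS v NZ the ceiling is 96 v 144 measurements per visit, power for a 20% reduction is about 74% instead of 83%, and the reduction detectable with 80% power is about 21.5% instead of 19%. The 30% and 40% scenarios are safe, and NZ v control is unaffected at its target size. The aim of covering all arms in every region is not met for CS.

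These figures rest on the plan's own simplifications: independent measurements, arithmetic means with a common SD of 5.8, two-sided .05, full recruitment to the plant cap and no baseline adjustment. A baseline correlation of about 0.37 or more would bring the CS contrasts back to 80%. Whether that can be expected is not shown. It would go too far to conclude that the CS arm cannot be evaluated, or that the departure was concealed.

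**What to change.** - Replace 1:1:1 with the actual allocation of 3 NZ, 2 CS and 3 control plants, and say that one plant is in no original arm.
- Replace the single figure of 144 per group and 432 in total with maxima per visit of 144, 96 and 144, or 384 across the arms.
- Give power and detectable reduction separately for NZ v control and for the two CS contrasts, with any gain from baseline adjustment shown as a range over a stated correlation.
- State that the ventilation plant is outside the arm contrasts and is not pooled with controls.
- Note that at least one region has no CS plant.

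The cost is wording and a short recalculation. No new data are needed. The CS figures become somewhat less favourable.

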## Discussion

### Preliminary Principal Findings

The response rate could not be calculated precisely as the project group did not have the opportunity to distribute questionnaires personally in all plants. Also, the seafood industry is an industry heavily relying on short-time and temporary labor, making it difficult to keep track of which employees are available for inclusion at any given time, as well as to supply questionnaires in the correct language. Difficulties in calculating exact response and participation rates is a known problem in research concerning occupational health in the seafood industry [41,42], and our average is in line with earlier studies with questionnaires in the Norwegian seafood industry [43].

In general, response or participation rates have been declining steeply over the past decades. It has been suggested to report several types of rates together with careful explanations about how they were calculated, rather than reporting single numbers, in order to give a more nuanced picture of the specific study [44].

### Strengths and Limitations

To our knowledge, this is the largest study on a salmon processing worker population assessing exposure to bioaerosols and its associations with respiratory and skin outcomes. Further, it is the first study to strategically test different measures of intervention for reducing bioaerosol levels.

The main strengths of the study include (1) its prospective design, with measurements of bioaerosol exposure and a range of health effects before and after implementation of exposure-reducing measures; (2) its multicenter design and provision of study material in 6 relevant languages, thereby covering a large and representative proportion of workers in the Norwegian salmon processing industry; (3) the large population size, with repeated sampling over consecutive work shifts and with a 1-year interval between measurements, which allows us to assess what affects the variability in exposure; and (4) extensive collection and analysis of active components in the bioaerosols, such as fish allergens, enzymes, and endotoxins, which will allow us to investigate which bioactive molecules and microbial agents are commonly present in bioaerosols produced during salmon processing, as well as respiratory and dermal health and health-promoting factors among salmon industry workers. The repeated measurements design allows analyses of paired samples, reducing the interindividual variation in samples assumed to show small changes in assumed healthy workers.

A special trait of the study is the combination of the assessment of work-related risk factors and work-related health-promoting factors which has so far not been done in the salmon processing industry.

For the health examinations, we cannot rule out a certain selection bias, as participation was restricted due to capacity reasons, as well as because it was voluntary. The latter could result in workers with existing health problems being more prone to participate, in order to find out more about their health, but it could also lead to refusal due to a fear of losing their job. The latter was addressed in the consent form and information meetings, emphasizing that employers of plant staff will not be informed about individual health findings. In any case, it is impossible to say in which direction this possible bias would influence results.

The lack of randomization to interventional categories is in part a weakness, but at the same time a necessary approach in order to make the study feasible. The seafood industry is in constant change and has to react quickly to challenges on the market. Therefore, it is unlikely to meet stable conditions over a longer time period, as this study confirmed. Also, as each plant’s infrastructure and needs are so different, it is not feasible to allocate the plants to predefined detailed interventions. Due to limited capacity, it will only be possible to include some of the participants in the different health examinations, and this will hamper the interpretation of associations between the different outcomes to a varying extent.

Another weakness is the pandemic-related delay in baseline measurements at 3 of the plants, which moved the period under study forward to a timeframe with a potentially lower production rate, warmer weather, and higher probability of pollen exposure outdoors, which could affect exposure measurements, as well as symptoms in the airways and skin. In order to keep circumstances somewhat similar, follow-up measurements at T_2_ are planned to be performed around the same time of the year.

All abovementioned factors will be further discussed in future publications for data from this study.

